### Recruitment and enrollment of participants

Subjects aged between 9 and 16 years who are enrolled in the compulsory education system in the territory of Mataró (Catalonia). Eligible patients have been identified following the EU General Data Protection Regulation (GDPR-2018) and then randomised and stratified by schools and institutes. These educational centres have a social class value (high/middle/low) assigned according to the MEDEA variable [37] and are differentiated by type (charter/private or public). A number of educational centres have been randomly selected from each social class-type combination, taking into account the number of students enrolled in each educational centre in order to reach the necessary sample that is representative of the students attending school in Mataró.

General practitioners and primary care nurses invite subjects to participate in the study from schools. Informative talks are held at the educational centres in which the legal guardians of the subjects are informed about the study and are requested to give their written informed consent for their children’s participation. Once subjects and/or their legal guardians accept to participate in the study, they are scheduled a visit at their own educational center where they are informed about the details of the study and enrolled if they meet the selection criteria outlined below.

*Inclusion criteria*: subjects between 9 and 16 years of age whose legal guardians have provided written informed consent for their children’s participation in the study. Subjects over 12 years of age are also required to give their own written informed consent.*Exclusion criteria*: subjects with previously diagnosed liver disease, receiving hepatotoxic drug treatment, with eating disorders diagnosed prior to study entry and/or children/adolescents who do not attend class on the day of the measurements.

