## Introduction

The increase of childhood obesity and its associated metabolic factors has led to an alarming rise in the incidence of non-alcoholic fatty liver disease (NAFLD) in this population. NAFLD is the accumulation of free fatty acids and triglycerides (TG) in the hepatocytes of individuals without toxic alcohol consumption and in the absence of other liver diseases. This pathology encompasses a wide spectrum of lesions ranging from simple steatosis to fibrosis, cirrhosis and even hepatocellular carcinoma [1].

NAFLD is the most common cause of liver disease and hypertransaminasaemia in the paediatric population, with a prevalence ranging from 7–9% and reaching 38–41% in obese children [2, 3]. Obesity is the main risk factor for NAFLD. The pathophysiological mechanisms are not yet fully understood, although the pathogenesis of NAFLD is considered to be multifactorial [4, 5]. The importance of early detection and appropriate management lies in its risk of progression to fibrosis and/or hepatocellular carcinoma along with its associated extrahepatic complications such as cardiovascular disease (CVD), diabetes mellitus (DM), insulin resistance (IR) and other endocrine and metabolic disorders like hypothyroidism or dyslipidaemia [6]. The presence of fibrosis is the major prognostic factor in NAFLD. Among children and adolescents with NAFLD, 25% have NASH and 14% have advanced fibrosis, the latter being more prevalent in paediatric patients with severe obesity than in adults with the same condition [7].

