Diet Quality estimation: KIDMED index [31] is used. It is based on 16 items with a dichotomous (yes/no) response format, and estimates adherence to the Mediterranean diet in children/adolescents. The index ranges from -4 to 12, and is based on a 16-question test. Answers are assigned a value of -1 or +1, respectively. The sums of these values are classified into 3 levels: a) >8, optimal diet; b) 4–7, improvement needed; c) <3, very low diet quality.PA assessment: PAU-7S [32] is used. PAU-7S consists of 7 questions referring to the week before the test. It takes different types of PA into consideration (walking; team sports; individual activity), as well as the context where it was practiced (schoolyard; after school and on weekends; physical education classes). The last question refers to whether the child was ill during the previous week or was unable to perform PA for some reason. Questions 1–6 are answered according to 5 possible options that refer to time spent (no activity, 0 minutes; <30 minutes; 30–60 minutes; 60–90 minutes; and >90 minutes. The questionnaire gives the total amount of minutes dedicated to PA in the week before the test is taken.Other child/adolescent lifestyle variables:
Sedentary behaviour is assessed by the Screen-time Sedentary Behaviour Questionnaire [33], which asks about time spent in: 1) watching TV, 2) playing computer games, 3) playing video games, 4) using mobile phone, separately for weekdays/weekends.Sleep duration is recorded by 4 questions on hours of sleep from the Sleep Habits Survey for Adolescents that ask about bedtime and time of waking up on weekdays/weekends [34].Consumption of sugar containing carbonated/no-carbonated beverages is assessed by standardized questions.

**Physical examination** is carried out by healthcare workers (minimum of 2) with participants in their underwear and barefoot.

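### Prevalence is presented as that of Mataró pupils and the general population, but entry depends on consent and attendance, and no adjustment for non-participation is stated

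*Protocol article*

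**What the plan says.** All references are to the protocol article.

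- **Sampling** (Recruitment and enrollment of participants): "A number of educational centres have been randomly selected from each social class-type combination", allowing for enrolment per centre, "in order to reach the necessary sample that is representative of the students attending school in Mataró". The same section also says that eligible pupils were identified and then randomised, with stratification by centre. It does not make clear whether pupils were also drawn at random within centres.
- **Entry** (same section): guardians attend an informative talk and "are requested to give their written informed consent". For older children, "Subjects over 12 years of age are also required to give their own written informed consent". A visit is booked only after acceptance: "Once subjects and/or their legal guardians accept to participate in the study". The exclusions include "children/adolescents who do not attend class on the day of the measurements".
- **Examination** (Data collection and measuring tools): the physical examination is done "with participants in their underwear and barefoot".
- **Target** (Main outcome measures): the percentages with LSM ≥6.5 kPa and CAP ≥225 dB/m are stated for the general population in the age range.
- **Analysis** (Statistical analyses): prevalences by sex and age group with 95% confidence intervals, hierarchical models when necessary because pupils come from selected schools, and no imputation because few further missing values are expected.
- **Losses allowed for** (Sample size calculation): blood available in 50% and MRI in 70%. No participation rate is given.
- **Link with weight** (Introduction): NAFLD is described "with a prevalence ranging from 7–9% and reaching 38–41% in obese children".

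**The concern.** Random selection of schools within social class and type supports representativeness at school level. It does not carry over to the children measured, because consent and attendance act after the draw. The main estimate is then a percentage among volunteers, labelled as that of a wider population.

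Two kinds of selection matter. Uptake may differ between schools, and so between social classes, ages or sexes. It may also be related to body weight. The second has leverage here, because the Introduction puts NAFLD about five times as high in obese children as overall (39.5/8 = 4.9, using the midpoints). An examination in underwear is one plausible route by which weight could influence consent.

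Hierarchical models deal with clustering within schools, not with who agreed to take part. The confidence interval reflects sampling error only, and a larger sample would not reduce the bias.

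**Working it through.** **1. The plan's own sample size.** Inputs from Sample size calculation: population 11,503 in four roughly equal strata (11,503/4 = 2,875.75 each), NAFLD 8% ± 2 points, fibrosis 2% ± 1 point, design effect 1.2.

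n0 = 1.96² p(1−p)/d², corrected to n0/(1 + (n0−1)/2,875.75), then × 1.2 × 4.

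- Fibrosis: 752.9 → 596.9 → 716.2 per stratum → 2,865 in total.
- NAFLD: 706.8 → 567.5 → 681.0 per stratum → 2,724 in total.

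The fibrosis target reproduces the stated 2,866 to within one. It is a count of examined pupils, and no participation term is needed to reach it.

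**2. Sampling error for comparison.** Whole sample: 1.96 × √(1.2 × 0.08 × 0.92/2,866) = 1.09 points (0.94 with the finite population correction). Planned per stratum: 2 points.

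**3. Size of a weight-related bias.** From the protocol: overall NAFLD 8%, and 39.5% in obese children (midpoint of 38–41%). Not in the protocol, so assumed: obese share o of 10–15%, and participation of obese children relative to others, r, varied on both sides of 1. I also assume that the Introduction's contrast applies to NAFLD as measured by CAP.

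- Prevalence in non-obese children: (8 − o × 39.5)/(1 − o) = 4.50% for o = 10%, and 2.44% for o = 15%.
- Obese share among participants: w = o·r/(o·r + 1 − o).
- Bias = (w − o) × (39.5 − non-obese prevalence).

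Example for r = 0.7:
- o = 10%: w = 0.07/0.97 = 7.22%; bias = −0.0278 × 35.0 = −0.97; measured 7.03%.
- o = 15%: w = 0.105/0.955 = 10.99%; bias = −0.0401 × 37.06 = −1.48; measured 6.52%.

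Measured prevalence when the true value is 8% (bias in points):

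| r | o = 10% | o = 15% |
|---|---|---|
| 0.5 | 6.34% (−1.66) | 5.45% (−2.55) |
| 0.7 | 7.03% (−0.97) | 6.52% (−1.48) |
| 0.9 | 7.68% (−0.32) | 7.52% (−0.48) |
| 1.0 | 8.00% (0) | 8.00% (0) |
| 1.1 | 8.31% (+0.31) | 8.47% (+0.47) |
| 1.3 | 8.92% (+0.92) | 9.36% (+1.36) |
| 1.5 | 9.50% (+1.50) | 10.20% (+2.20) |

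Using 38% or 41% in place of 39.5% moves these entries by at most about 0.13 points.

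**4. Reading.** For r of 0.7–0.9 the bias is 0.3–1.5 points downward, and for r of 1.1–1.3 it is 0.3–1.4 points upward. At the outer end this is comparable with, or larger than, the whole-sample half-width. It stays within the 2 points planned per stratum. In this table only r = 0.5 or r = 1.5 combined with 15% obesity goes beyond that.

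**The case against.** - **A reader might infer that NAFLD prevalence will come out too low.** The documents do not support that. Nothing in them shows that obese children decline more often. Recruitment is by talks about the study, and participants receive a liver scan and lifestyle counselling, so worried families may join more readily. This stands: the direction is open.
- **Randomness may not stop at schools.** The recruitment section also mentions randomising eligible pupils, so it would be wrong to say that only schools were drawn at random. This stands too, but consent and attendance would still act after any pupil-level draw.
- **The representativeness phrase states the purpose of drawing schools, not a result.** This is partly right. The main outcomes nevertheless carry the general-population label without qualification.
- **Weighting may be in an analysis plan that is not shown.** It may, and its absence from an article is not in itself an error. The point rests on the population claims set against the entry process described beside them. The remark about few missing values reads most naturally as concerning enrolled children, so it settles nothing about decliners.
- **The blood test might be thought to deter entry to the prevalence sample.** That carries little weight. CAP and LSM are measured at Visit 1 and blood is taken at Visit 3, so a child without a blood sample still counts.
- **Any consent-based school survey has this problem.** True, and consent is unavoidable. That is a reason to qualify the claim and show its sensitivity, not to leave it unqualified.

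**Conclusion.** The point holds as a moderate one. As written, an unadjusted percentage among consenting, attending pupils would be reported as the prevalence in Mataró pupils or the general population. The resulting bias has unknown sign. Its size is about 0.3–1.5 points on an 8% prevalence, if 10–15% of pupils are obese and they take part at 0.7–0.9 times the rate of others, and similar in the upward direction if they take part more. Both inputs are assumptions, and with equal participation by weight this bias is zero. Under these assumptions the error can match the overall sampling error but not the planned precision per stratum. The case for change is that the interval cannot reveal the error and that the remedy is cheap, not that bias has been shown.

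**What to change.** 1. **Statistical analyses:** record eligible, consenting and measured pupils by school (social class × type), age group and sex. Start from the enrolment figures already used to select centres, and weight the prevalence estimates to the school roll in these cells. The article confirms that enrolment per centre was used. It does not say that counts by age and sex within centre, or counts of decliners, are kept, so these may have to be obtained from the schools.
2. **Sensitivity analysis:** cell weights do not correct refusal related to weight among children of the same school, age and sex. Add one analysis that gives obese participants, by a prespecified definition based on measured BMI, a further weight of 1/r, with r on both sides of 1, for example 0.5 to 1.5.
3. **Main outcome measures and Recruitment and enrollment of participants:** limit the word representative to the selection of schools, and describe the unadjusted figure as prevalence among participating pupils.

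Cost: slightly wider confidence intervals from the weights, and a little more record keeping and analysis. No new measurement of participants is needed.

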### Main outcome measures

Percentage of subjects with LSM ≥6.5 kPa by VCTE in the general population aged ≥9 to ≤16 years.Percentage of subjects with CAP ≥225 dB/m by VCTE in the general population aged ≥9 to ≤16 years.Comparison of liver steatosis diagnosis accuracy between CAP by VCTE and MRI in the general population aged ≥9 to ≤16 years.Determination of optimal cut-off points of the CAP for the diagnosis of mild, moderate and severe liver steatosis in children and adolescents.

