### Data collection and measuring tools

Data are being collected from November 2022 to June 2023, in educational centres, primary care centres and diagnostic imaging centres. Organisation of data collection follows the procedure outlined in Table 1.

**Table 1 pone.0286586.t001:** Organisation of data collection procedures.

	Visit 1	Visit 2	Visit 3	Visit 4	Visit 5
	At educational centres	At primary care centres	At educational centres	At Diagnostic Imaging Centres	At the HUGTIP Hospital
Selection criteria					
Informed Consent					
Socio-demographic data					
Anamnesis and clinical history					
Physical examination					
Analytical determination					
Lifestyle assessment					
VCTE					
MRI					
Diagnostic tests / follow-up according to usual clinical procedure					

VCTE, Vibration-Controlled Transient Elastography; MRI, Magnetic resonance imaging.

**Socio-demographic data** include: age, sex, household income, parents’ education level, educational centre.

**Anamnesis and clinical history** include:

Comorbidities and pathological history: AHT, DM, dyslipidaemia, obesity or any other chronic diseases.Alcohol consumption: in standard drinking units (SDU).Tobacco consumption.Regular use of medication and/or other toxics.Family clinical history: family history of obesity, NAFLD, AHT, DM, dyslipidaemia and CVD.

**Lifestyle assessment** is self-reported online at the participating schools with the assistance of trained personnel.

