### Statistical analyses

Prevalences of NAFLD and fibrosis will be calculated using CAP ≥225dB/m and LSM ≥6.5kPa, respectively. They will be calculated by sex and age (9–12 and 13–16 years) and 95% confidence intervals will be provided.To determine the optimal CAP cut-off point that best fits the 4 MRI categories, the relationship between CAP and MRI will be explored graphically, CAP means for each MRI category will be compared by ANOVA, 2-to-2 ROC curves will be used, and a multi-class ROC curve will be used to obtain the overall area under the curve for the finally chosen points. In addition, dichotomous CAP classifications (normal/altered) will be compared with MRI levels using contingency tables and chi-square tests.To identify the variables related to NAFLD, multivariate models will be used using NAFLD as the dependent variable and possible risk and confounding factors as independent variables.Concordance between the diagnosis of NAFLD or fibrosis obtained by different methods (CAP vs FLI, LSM vs PNFI, LSM vs PNFS) will be assessed by kappa indices (when using the dichotomised version of these variables) and by the intraclass correlation coefficient (when using the continuous version of the variables). The best cut-off point in PNFI and PNFS will be chosen to detect fibrosis using LSM ≥6.5 kPa as the standard test in the diagnosis of fibrosis using ROC curves.The construction of the biomarker to detect the presence of steatosis in children and adolescents will be carried out using the coefficients of multivariate logistic regression models, where steatosis (CAP >225 dB/m) will be the dependent variable and the rest of the variables will be potential explanatory variables that may form part of the marker.

To take into account that participants come from selected schools, hierarchical models will be used when necessary. All tests will be bilateral, with a significance of 5%. We do not plan to use missing data imputation methods as we expect very few missings beyond those already considered. Stata17 statistical package will be used.

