## Expected results

As regards the direct results related to the main objectives of this project, it is expected to be obtained that: 1) the prevalence of liver fibrosis is around 2% and that of NAFLD is around 8% among the general population aged 9–16 years; 2) the degree of NAFLD can be estimated by the CAP in a form analogous to that of MRI in children and adolescents.

The project will provide essential information on childhood NAFLD. That is particularly relevant as we are at a time when the burden of chronic liver diseases is on the rise and, moreover, it is expected to increase in the coming years. The results of this project with the exhaustive tests will allow (1) to assess the current prevalence of both NAFLD and liver fibrosis in the general population between 9 and 16 years, (2) to understand in further detail the comorbidities associated with childhood obesity and to identify the risk groups of children and adolescents who, without being obese, may be at risk of developing NAFLD or any of its complications and (3) the validation of VCTE as a non-invasive, simple and safe method to progress in the early diagnosis of chronic liver diseases in an easy and safe way in a highly vulnerable population such as paediatrics. Hence, this project will allow the development of strategies and algorithms adapted to the infant-juvenile population, enabling the early diagnosis of NAFLD from a much earlier age.

In addition, the LiverKids study will serve as a basis from which to generate a population cohort that can be followed in the long term to obtain more information on the evolutionary course of NAFLD from childhood onwards.

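### Children with known NAFLD are screened out of a study that reports NAFLD and fibrosis prevalence in the general population, so as written it estimates undiagnosed disease

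*Protocol article*

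**What the plan says.** All references are to the protocol article.

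- **Exclusion.** Recruitment and enrollment of participants excludes "subjects with previously diagnosed liver disease, receiving hepatotoxic drug treatment, with eating disorders diagnosed prior to study entry". Nothing there exempts NAFLD.
- **NAFLD as a liver disease.** The Introduction states that "NAFLD is the most common cause of liver disease and hypertransaminasaemia in the paediatric population".
- **What is to be estimated.** Main outcome measures lists "Percentage of subjects with LSM ≥6.5 kPa by VCTE in the general population aged ≥9 to ≤16 years" and "Percentage of subjects with CAP ≥225 dB/m by VCTE in the general population aged ≥9 to ≤16 years". Expected results says the study will allow the team "to assess the current prevalence of both NAFLD and liver fibrosis in the general population between 9 and 16 years". Study aims gives the same two prevalences as aim 1, without limiting them to undiagnosed children.
- **Case definition.** The Introduction describes NAFLD as fat accumulation in "individuals without toxic alcohol consumption and in the absence of other liver diseases". Statistical analyses says: "Prevalences of NAFLD and fibrosis will be calculated using CAP ≥225dB/m and LSM ≥6.5kPa, respectively". Alcohol intake is recorded in standard drinking units (Data collection and measuring tools), but it appears neither among the exclusions nor in that calculation.

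**The concern.** A prevalence covers everyone with the condition, whether or not it has been recognised. A child with known NAFLD, or with known fibrosis from it, belongs to the population that the outcomes name, yet the exclusion bars that child. The target is then total prevalence, while the estimator gives undiagnosed prevalence among eligible pupils. A larger sample does not remove this difference.

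The loss is also unlikely to be random. The Introduction says the diagnosis should be considered above all in children with excess weight, hypertension, diabetes, insulin resistance or metabolic syndrome. Known cases may therefore cluster in the risk groups that the study hopes to identify.

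The second, smaller matter is a label. The Introduction's definition rules out toxic alcohol consumption, but the Abstract, Study aims and Statistical analyses call CAP ≥225 dB/m NAFLD with no alcohol condition. Study design even lists risky alcohol use among NAFLD risk factors.

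**Working it through.** **Inputs from Sample size calculation:** population 11,503 in four roughly equal strata, so N = 11,503/4 = 2,875.75 per stratum; NAFLD 8% ± 2 points and fibrosis 2% ± 1 point in each stratum; design effect 1.2; two-sided 5% (z = 1.96); total 2,866.

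**Assumed, because the documents give no figure:** s, the share of cases already diagnosed.

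**1. The plan's own figure.** n0 = z²p(1−p)/d², with finite population correction n0/(1 + n0/N), then × 1.2 × 4.

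- Fibrosis: n0 = 1.96² × 0.02 × 0.98 / 0.01² = 752.9; corrected 596.7; × 4.8 = 2,864. Rounding up to 597 per stratum first gives 597 × 4.8 = 2,865.6, or 2,866.
- NAFLD: n0 = 706.8; corrected 567.4; × 4.8 = 2,723.

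The stated 2,866 reproduces, with fibrosis setting the size. The sample size is not in question. The planned 8% lies inside the 7–9% that the Introduction gives for paediatric prevalence, with no visible deduction for known cases.

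**2. Effect of the exclusion.** If a share s of true cases is removed before measurement, and those children would have met the threshold if measured:

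observed = p(1 − s) / (1 − p·s)

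For example, with p = 0.08 and s = 0.10: 0.072 / 0.992 = 7.26%.

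| s (assumed) | NAFLD, true 8% | Shift (points) | Fibrosis, true 2% | Shift (points) |
|---|---|---|---|---|
| 5% | 7.63% | 0.37 | 1.90% | 0.10 |
| 10% | 7.26% | 0.74 | 1.80% | 0.20 |
| 20% | 6.50% | 1.50 | 1.61% | 0.39 |

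**3. Comparison with sampling error.** Half-width = z√[p(1−p) × 1.2/n × (1 − n/N)].

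- Overall (n = 2,866, N = 11,503): 0.94 points for NAFLD and 0.49 for fibrosis. The shift reaches these at s of about 13% and 25%.
- Per stratum (n = 716.5, N = 2,875.75): 1.89 and 0.97 points. The shift reaches these at s of about 25% and 50%.

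Over the assumed range, the shift stays below the stated per-stratum precision of 2 points and 1 point. It exceeds the overall half-width for NAFLD once s passes about 13%.

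**4. Alcohol.** Suppose 5% of children drink at a risky level (an assumption) and have the same 8% rate of CAP ≥225 dB/m. Removing them from numerator and denominator gives (0.08 − 0.05 × 0.08)/(1 − 0.05) = 0.076/0.95 = 8%, so there is no change. A shift arises only if their rate differs from the rest, and the documents say nothing on that.

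**The case against.** Much of the case on the other side stands.

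- **The diagnosed share may be small.** Study rationale and hypotheses says no early-detection strategies exist for this population. The Introduction adds that transaminases may be normal, that ultrasound sees only fat above 30% and that biopsy use is limited. A reader might take a 50% diagnosed share for fibrosis, which would turn 2% into 1.0% and use up the stated 1-point precision. Nothing in the text supports a share that high.
- **The exclusion partly fits the study.** Leaving out other liver disease follows the Introduction's definition of NAFLD, and the first hypothesis concerns asymptomatic children. But aim 1 and the main outcomes are not confined to undiagnosed children. If only other liver disease was meant, the criterion does not say so.
- **The literal steatosis outcome is the percentage with CAP ≥225 dB/m.** That outcome needs no alcohol condition. The mismatch therefore affects only the NAFLD label. A reader might multiply an assumed 5% of risky drinkers by 8% and claim a 0.4-point excess. That figure arises only if they leave the numerator and stay in the denominator, and it should not be claimed.
- **Wider harm is not shown.** A reader might infer that the CAP–MRI comparison or the risk-factor models are damaged. No figure shows this, and all enrolled children with a positive CAP or LSM are still sent for MRI.

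What the objection does not answer is the wording itself: an exclusion without exemption beside outcomes stated for the general population.

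**Conclusion.** The point holds in limited form. As written, the study estimates the prevalence of NAFLD and fibrosis among children without known liver disease, and this understates the general-population figures it promises. The direction follows from the design. The size does not: it rests on an assumed diagnosed share, and on known cases still meeting the CAP or LSM threshold. With 5% to 20% of NAFLD cases known, 8% becomes 7.6% to 6.5%. With 10% to 20% of fibrosis cases known, 2% becomes 1.8% to 1.6%. This is worth correcting because it touches both main prevalences and costs little. The documents do not support the stronger reading that these prevalences are invalid.

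The alcohol matter survives only as a mismatch between the Introduction's definition and the NAFLD label used elsewhere. Its effect is probably small.

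**What to change.** 1. Limit the exclusion to previously diagnosed liver disease other than NAFLD. Measure children with known NAFLD at Visit 1 like all others, flag them, and report each prevalence with and without them. Known fibrosis from other liver disease would still be excluded, so the fibrosis result should say so.
2. For children already screened out, report how many were excluded for known NAFLD or fibrosis. Show their add-back only as a sensitivity figure. They have no study CAP or LSM, so adding them mixes earlier diagnoses made by other methods with the study's thresholds.
3. If known cases cannot be included, call the estimate the prevalence among children without known liver disease in the outcomes and conclusions.
4. Report CAP ≥225 dB/m as CAP-defined steatosis, or apply the recorded alcohol data before using the term NAFLD, and reconcile this with the Introduction's definition.

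The cost is a short amendment while recruitment is under way, one database flag, and two prevalence figures where there was one. The added children need no new procedure.
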